**Fig. 3 Fig3:**
[figure not shown]
Custom-made abdominal corset (Heerkens et al. Physics and imaging in Radiation oncology. 2017)

For this study, the clinical target volume (CTV) equals the gross tumor volume (GTV), including the tumor in the pancreas and immediately adjacent involved lymph nodes. The planning target volume (PTV) will be generated by adding a margin of 3–5 mm around the GTV depending on institutional protocols. The duodenum, bowel stomach, liver, kidneys, and spinal cord will be contoured as avoidance structures. Limits of the maximum doses to critical structures such duodenum, bowel and stomach are prioritized.

Generally, patients receive dietary instructions as treatment will be delivered after 2 hours fasting. Patients may be pre-medicated (2 hours before each fraction) with ondansetron and/or dexamethasone in order to prevent radiation-induced early side effects, or aggravation of pain. In case of intolerance or severe complaints, modification or discontinuing the radiation plan can be necessary.

All radiation-associated early and late toxicity will be scored according to the NCI-CTCAE toxicity criteria version 5.0 [22]. Potential acute toxicity (within three months) that particularly will be noted are fatigue, pain, nausea, vomiting and diarrhea. Regarding toxicity after three months (late toxicity), particular attention will be paid to complaints of the stomach or duodenum, complaints, such as dyspepsia, bleeding, or perforation.

After completion of the last SABR fraction, questionnaires will be filled in, and all end-of-treatment forms. Patients must be seen by the radiation oncologist at the day of the last fraction. Patients in the SABR arm will be contacted additionally at 3 and 6 weeks by the radiation oncologist for acute toxicity. Follow-up with respect to disease status, performance status and quality of life will be performed by telephone and (e-)mail through PACAP at the fixed study assessment points, which coincide with the time points for follow up during best supportive care.

Primary endpoint is the overall survival rate from the date of randomization. Secondary endpoints include time to a decrease in global quality of life (QoL, using the QLQ- C30 and EORTC-PAN26 questionnaires), pain response by using the Numerical rating Scale (NRS), CA19.9 response, and acute and subacute toxicity rates using common toxicity criteria (NCI-CTCAE toxicity criteria version 5.0).

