Based on previous literature and our own experience, we assume that at 6 months from the date of randomization, 50% of patients treated with SABR will be alive versus 20% of patients managed with best supportive care [4, 11]. Taking into account that an estimated 30% of patients randomized for the intervention arm will ultimately refrain from SABR, this will dilute the expected survival in the intervention arm to 41% (0.7 × 50% + 0.3 × 20%). Since the control arm is not informed about the intervention, we assume 100% compliance in this arm. Because this phase 2 study will constitute preliminary outcomes for further studies, it is considered not as bad to unjustly reject the null hypothesis (i.e. Finding an effect that actually exists is more important than to wrongly find an effect). Therefore we use and alpha of 15% instead of 5%. Following calculation of the sample size with alpha 15% and power 80%, 49 patients per treatment arm are required in this randomized trial [23].

Randomization will be stratified according to the reason for not undergoing surgery and/or systemic chemotherapy in order to ensure an even distribution of patients with potentially better prognosis who had refused chemotherapy and/or surgery in both study arms. Patients will be randomized using a secured online computer controlled permuted-block randomization in a 1:1 ratio (CASTOR EDC, CIWIT B.V., Amsterdam, The Netherlands). The block sizes itself will are prone to randomly change, varying between 4, 6 and 8 patients.

According to the TwiCs design, patients will be informed about randomization to the intervention (SABR) within this trial by either the local principal investigator or the coordinating physician. Furthermore, they will be informed that they are free to decide whether they want to adhere or deny this intervention. If they choose to adhere to the assigned treatment arm, written informed consent will be obtained in addition to verbal information, by the local principal investigator before the start of SABR. After signing informed consent, patients should receive the first fraction of SABR within four weeks. Participants in the PACAP-cohort who have been randomized for the control arm, i.e. best supportive care, will be treated and followed according to the current standard of care.

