Data will be collected using a secured electronic database (CASTOR EDC, CIWIT B.V., Amsterdam, The Netherlands) by the coordination physician and a clinical data manager. All variables mentioned in the inclusion criteria will be analyzed and reported using standard descriptive statistics. Continuous variables will be summarized with standard statistics including means, standard deviations, medians and ranges. Categorical variables will be summarized with frequencies. When appropriate, box plots and cross tables will be used for descriptive statistics of continuous and categorical variables, respectively. Survival endpoints will be analyzed using log rank tests and Kaplan Meier plots, additionally Cox proportional hazards models are used in order to adjust for stratification and prognostic variables. *P*-values below 0.05 will be considered significant. All calculations will be generated by statistical package for social sciences software (IBM SPSS v.28).

Data will be handled confidentially. An individual subject identification code is used to link the data to the subject. A code is generated based on the first three letters of the month of inclusion and a sequential number. The study coordinators safeguard the key to the code and access to the coded data will be restricted to the principal investigators, the coordinating investigator, the study coordinators and the monitor. The handling of personal data will comply with the General Data Protection Regulation (in Dutch: Algemene vordering gegevensbescherming (AVG)). The principal investigators will keep the source data for 15 years.

Any modifications to the protocol which may impact on the conduct of the study, patients safety, potential benefit of the patient, including changes of study objectives, inclusion criteria, sample sizes, study procedures, will require an amendment to the protocol. If the study staff will concur with such amendment, approval of the Institutional Medical Ethics Review board of VU University Medical Center in Amsterdam is necessary prior to implementation. Important protocol modification will be communicated by electronic newsletters and additional site visits if necessary.

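### Randomisation is stratified by a factor thought to be prognostic, but the survival test reads as a plain log-rank, with that factor entering only an additional, unranked Cox model

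*Protocol article*

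**What the plan says.** All of this is in the Methods/design section of the protocol article.

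- **Endpoint.** "Primary endpoint is the overall survival rate from the date of randomization".
- **Randomisation.** "Randomization will be stratified according to the reason for not undergoing surgery and/or systemic chemotherapy". The stated purpose is to spread evenly the "patients with potentially better prognosis who had refused chemotherapy and/or surgery in both study arms". Allocation is 1:1 in permuted blocks of 4, 6 and 8. The levels of the factor are not listed.
- **Survival analysis.** "Survival endpoints will be analyzed using log rank tests and Kaplan Meier plots". The same sentence continues: "additionally Cox proportional hazards models are used in order to adjust for stratification and prognostic variables".
- **Sample size.** The assumption at 6 months is that "50% of patients treated with SABR will be alive versus 20% of patients managed with best supportive care". Because 30% of the intervention arm is expected to decline SABR, the 50% is diluted to 41%. With alpha 15% and power 80% this gives 49 per arm.

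The article does not call the log-rank test stratified or unstratified, and it does not say whether the log-rank test or the Cox model decides the primary comparison.

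**The concern.** The survival sentence assigns adjustment for the stratification factor to the Cox model and adds that model to the log-rank test. A reader would take this as a plain log-rank test in the lead with an adjusted model beside it.

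Permuted blocks within strata hold the arms nearly balanced on the factor. The variance formula of the plain log-rank test does not know this: it still allows for chance imbalance that the design has removed. If the factor affects survival, that variance is too large. The test then rejects less often than its nominal level and gives up power. The plain test also compares patients across strata of different risk, which weakens the apparent treatment effect.

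At stake are some power in a trial of 98 patients, whose alpha was relaxed in order to reach 80%, and a clear answer on overall survival. Two planned analyses with no order between them can point in different directions.

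**Working it through.** **1. The plan's own figure.** The 49 per arm reproduces as a two-sided comparison of 41% with 20%, by the arcsine formula:

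- h = 2·asin(√0.41) − 2·asin(√0.20) = 1.3898 − 0.9273 = 0.4625
- n = 2·(z₀.₉₂₅ + z₀.₈₀)² / h² = 2·(1.4395 + 0.8416)² / 0.2139 = 48.65, rounded up to 49

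The pooled normal formula gives 50. Both compare proportions at 6 months, so the stated sample size does not depend on whether a log-rank test is stratified.

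**2. The two tests.** Let U be the sum over deaths of observed minus expected in the SABR arm, and V its hypergeometric variance.

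- Plain: Z = U/√V over all 98 patients.
- Stratified: Z = ΣUₛ/√ΣVₛ, computed within each stratum s and summed.

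**3. Simulation inputs.**

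- From the article: 49 per arm; 1:1 permuted blocks of 4, 6 and 8 within strata; 6-month survival of 20% against 41%.
- Assumed, because the article does not give them: exponential survival; two strata (refused, unfit); refuser share p of 30% or 50%; refuser hazard ratio θ from 1 to 0.33; censoring at 12 months, the last listed assessment.
- Calibration: the unfit-stratum hazard λ solves p·exp(−6λθ) + (1−p)·exp(−6λ) = 0.20. The treatment hazard ratio then solves the same equation for 0.41 (0.554 when θ = 1).
- 8,000 trials per setting, so the simulation error is about 0.4 points. Tests are two-sided; the article does not state the sidedness, but two-sided reproduces its sample size.

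**4. Results.** Each cell gives the values for a refuser share of 30% / 50%, in per cent.

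| θ (fold difference) | Plain, actual error at 15% | Power at 15%: plain | Power at 15%: stratified | Power at 5%: plain | Power at 5%: stratified |
|---|---|---|---|---|---|
| 1 (none) | 14.7 / 16.0 | 90.6 / 90.8 | 90.0 / 90.5 | 77.9 / 79.6 | 77.1 / 78.5 |
| 0.67 (1.5) | 15.0 / 15.0 | 90.7 / 91.5 | 91.3 / 92.0 | 78.0 / 79.5 | 79.0 / 80.5 |
| 0.5 (2) | 13.8 / 13.9 | 90.5 / 91.1 | 92.4 / 93.1 | 77.6 / 78.7 | 81.5 / 82.5 |
| 0.33 (3) | 10.5 / 11.4 | 90.5 / 92.1 | 95.0 / 96.3 | 77.2 / 80.0 | 86.9 / 89.8 |

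The stratified test's actual error at nominal 15% is 14.5–15.8% throughout. Both alphas are shown because the sample size uses 15% while the analysis text declares significance below 0.05. That mismatch is a separate matter.

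- 2-fold difference: the gain is 1.9–2.0 points at 15% and 3.8–3.9 at 5%.
- 3-fold difference: the gain is 4.2–4.5 points at 15% and 9.7–9.8 at 5%.
- 1.5-fold difference: 0.5–0.6 points at 15% and 1.0 at 5%.
- No difference: stratifying loses 0.3–0.6 points at 15% and 0.8–1.1 at 5%.

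**5. Two sensitivity checks.** With four strata of which only refusers differ, the gain at a 2-fold difference shrinks to about 1 point or less at 15% and about 1–3 points at 5%. With a weak factor and four strata, stratifying loses roughly 1–3 points. In two-stratum trials with a true effect, the plain and stratified tests gave opposite verdicts at 5% in about 6% of trials (2-fold) to 11–12% (3-fold).

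**The case against.** The strongest reply is that nothing here is stated wrongly. The article says only that log-rank tests will be used; that they are unstratified is inferred from the wording. A journal article may leave the exact form of the test, and the order of the analyses, to the full protocol or the SAP. The plan does use the factor, in the Cox model. The harm depends on a prognostic strength and a stratum share that the documents do not give, and at a 1.5-fold difference it all but vanishes. With many levels of the reason for no treatment (the Background lists patient's choice, extensive disease, functional status and high age), stratifying can cost power.

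Most of this stands and limits the point. What it does not remove is that the article goes beyond silence: it names the test and says where the stratification factor enters, and that place is the additional model.

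A reader might also infer more than the documents support:

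- *That the plan ignores its stratification factor.* It does not; the Cox model adjusts for it.
- *That the true type I error is below nominal as a fact.* It is visibly lower only if the factor is strong: about 14% at a 2-fold difference and 10.5–11.4% at 3-fold, but 15% at 1.5-fold.
- *That the trial is underpowered for this reason.* Under the assumptions above, the plain log-rank test keeps about 90% power at 15%, above the planned 80%.
- *That false positives become more likely.* The error runs in the conservative direction.

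**Conclusion.** The point holds as a modest improvement to the stated analysis. The primary survival test, as it reads, does not follow the stratified randomisation, and no analysis is ranked first. For two strata with a 2- to 3-fold hazard difference and 12-month censoring, the plain test has an actual error of about 11–14% at nominal 15%. Stratifying it would add about 2–5 points of power at 15% and 3–10 points at 5%. If the difference is 1.5-fold or smaller, there is almost nothing to gain. The documents call the factor only potentially prognostic, so its place in this range cannot be fixed from them. That the log-rank test is plain is a well-grounded inference, which a full protocol or SAP could overturn.

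**What to change.** State in the analysis section that the primary test of overall survival is the log-rank test stratified by the randomisation factor, and that the hazard ratio comes from a Cox model stratified by the same factor. Define the factor with few levels, for example refused versus unfit, matching those used at randomisation. Keep the unstratified log-rank test and the Cox model with further prognostic variables as supportive analyses. If the full protocol or SAP already says this, bring the article's wording into line with it.

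The change takes one or two sentences and needs no new data and no change to the 49 per arm. The cost is a loss of roughly 1–3 points of power if the factor proves weak or is split into many levels.

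### The trial is sized on a 15% alpha but the analysis paragraph declares significance at 0.05, so a primary p-value between the two has contradictory verdicts

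*Protocol article*

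**What the plan says.** The protocol article sets its threshold twice, both times in Methods/design.

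- **Sample-size paragraph.** It argues that for a phase 2 study meant to inform later work "it is considered not as bad to unjustly reject the null hypothesis", and concludes: "Therefore we use and alpha of 15% instead of 5" [per cent]. The planning rates at 6 months are "50% of patients treated with SABR will be alive versus 20% of patients managed with best supportive care". With 30% of the intervention arm expected to decline SABR, the intervention rate is diluted to 41%; the control rate stays at 20% because "we assume 100% compliance in this arm". The result is: "with alpha 15% and power 80%, 49 patients per treatment arm are required in this randomized trial".
- **Statistical-analysis paragraph.** It assigns log-rank tests, Kaplan-Meier plots and additional Cox models to the survival endpoints. The next sentence says that P-"values below 0.05 will be considered significant".

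The primary endpoint is overall survival from randomization, so it is one of the survival endpoints that the second paragraph covers. Neither paragraph states whether its threshold is one-sided or two-sided.

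**The concern.** The analysis paragraph brings back the 5% level that the sample-size paragraph considered and set aside. Both rules are in current text, and both reach the primary endpoint.

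The verdict on the primary endpoint is at stake. With p = 0.10, the trial succeeds by the rule it was sized on and fails by the rule in its analysis paragraph. If this is left open, the choice could be made once the result is known. There is also a consequence for power: 80% was calculated at 15% and does not carry over automatically to 0.05.

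**Working it through.** **Inputs from the sample-size paragraph.** p1 = 0.7 × 0.50 + 0.3 × 0.20 = 0.41; p2 = 0.20; difference 0.21; 49 per arm; power 80%; alpha 0.15. The analysis paragraph gives 0.05.

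**Step 1: reproduce the 49.** Two-proportion formula with pooled variance under the null hypothesis:

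n = [z_α √(2·p̄·(1−p̄)) + z_β √(p1(1−p1) + p2(1−p2))]² / (p1 − p2)²

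with p̄ = 0.305, √(2 × 0.305 × 0.695) = 0.6511, √(0.2419 + 0.1600) = 0.6340 and z_β = 0.8416.

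| Alpha | z_α | n per arm |
|---|---|---|
| 0.15 two-sided | 1.4395 | (0.9373 + 0.5336)² / 0.0441 = 49.06 |
| 0.15 one-sided | 1.0364 | (0.6748 + 0.5336)² / 0.0441 = 33.1 |
| 0.05 two-sided | 1.9600 | (1.2762 + 0.5336)² / 0.0441 = 74.3 |

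The stated 49 matches two-sided 15%. Strict rounding up of 49.06 gives 50; the arcsine version gives 48.7, hence 49; the unpooled version gives 47.4, hence 48. One-sided 15% is far off.

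**Step 2: power at 49 per arm on the same basis.** Power = Φ[(0.21 × √49 − z_α × 0.6511) / 0.6340].

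- Two-sided 0.15: Φ[(1.470 − 0.937) / 0.634] = Φ(0.840) = 80.0%.
- Two-sided 0.05: Φ[(1.470 − 1.276) / 0.634] = Φ(0.306) = 62.0%.
- One-sided 0.05 (z = 1.6449): Φ[(1.470 − 1.071) / 0.634] = Φ(0.629) = 73.5%.

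Exact enumeration of the chi-square test gives 80.8% at two-sided 0.15 and 62.2% at two-sided 0.05.

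**Step 3: chance of a p-value between the two thresholds.** Under the planned effect on this basis: 80.0% − 62.0% = 18%. Under no effect: 15% − 5% = 10%.

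**Step 4: the planned log-rank test.** This step needs assumptions that the article does not state: proportional hazards, exponential survival, and everyone followed for the period shown.

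- Hazard ratio = ln 0.41 / ln 0.20 = 0.554, so |ln HR| = 0.5906.
- Deaths by 6 months: 49 × (0.59 + 0.80) = 68.
- Deaths by 12 months: 49 × (1 − 0.41² + 1 − 0.20²) = 88.
- Deaths by 24 months: 49 × (1 − 0.41⁴ + 1 − 0.20⁴) = 96.5.
- Schoenfeld power = Φ(√D / 2 × 0.5906 − z_α).

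| Follow-up | Deaths | Power at two-sided 0.15 | Power at two-sided 0.05 | Chance that p is between |
|---|---|---|---|---|
| 6 months | 68 | 84% | 68% | 16% |
| 12 months | 88 | 91% | 79% | 12% |
| 24 months | 96.5 | 93% | 83% | 10% |

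**The case against.** The strongest objection concerns power. A reader might infer that applying 0.05 takes away the stated 80% and leaves 62%. The documents do not support that as a general statement. The 62% belongs to a comparison of proportions at 6 months, which is how the trial was sized, whereas the planned test is a log-rank test that also uses deaths after 6 months. Under the assumptions in step 4, its power at 0.05 is close to 80% by 12 months and above it by 24 months. The abstract schedules secondary and toxicity assessments to 12 months, but the article gives neither a survival follow-up length nor an event target. A power shortfall is therefore not demonstrated for the planned test. Equally, the article does not show that 80% is kept. A figure of 75 per arm for 80% power at two-sided 0.05 has the same limit: it holds for the 6-month comparison only.

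Two smaller points also stand. Sidedness is inferred from reproducing 49, not stated, and a one-sided 7.5% level would give the same number. The 0.05 sentence does not say that it covers every test; it is a general sentence without an exception.

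It could also be said that 0.05 was meant for secondary analyses, or that an analysis plan not shown here settles the matter. The first is not what the text says, since the sentence directly follows the survival methods. The second would answer an omission, but this is a conflict between two stated values, and a further document cannot make both of them hold.

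**Conclusion.** The contradiction stands and rests on the two paragraphs alone. The article has no single success criterion for overall survival when p lies between 0.05 and 0.15. Under the planned effect this happens with a chance of about 18% on the sample-size basis, or about 10–16% for a log-rank test (about 12% with 12 months of follow-up); under no effect the chance is 10%.

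The effect on power is conditional. On the plan's own basis, power falls from 80% to 62% if 0.05 is two-sided, or to 73.5% if it is one-sided. For the log-rank test at two-sided 0.05 it is about 68%, 79% or 83% with 6, 12 or 24 months of follow-up, given a constant hazard ratio of 0.554 and exponential survival. These assumptions affect the size of the problem but not its existence. Because it decides how the primary result is read, it must be corrected.

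**What to change.** In the statistical-analysis paragraph, state one alpha and its sidedness for the primary overall-survival test, and limit 0.05 to the rest. For example: *The primary overall-survival comparison is tested at the two-sided 15% level used for the sample size; the 0.05 threshold applies only to the other analyses.* The sponsor should confirm that two-sided was intended.

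If the sponsor prefers 0.05 for the primary test, the power statement must change with it: 62% at two-sided 0.05 on the stated basis, in place of 80%. A log-rank power could be given instead if the follow-up and hazard assumptions behind it are stated. The choice should be recorded before the interim analysis, which includes the primary outcome.

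The cost is one sentence and no patients. The downside of keeping 15% is that a positive result is weaker evidence, which the sample-size paragraph already accepts for a phase 2 study.

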**Methods:**

A nationwide multicenter trial performed within a previously established large prospective cohort (the Dutch Pancreatic cancer project; PACAP) according to the ‘Trial within cohorts’ (TwiCs) design. Patients enrolled in the PACAP cohort routinely provide informed consent to answer quality of life questionnaires and to be randomized according to the TwiCs design when eligible for a study. Patients with localized PDAC who are unfit for chemotherapy and surgery or those who refrain from these treatments are eligible. Patients will be randomized between SABR (5 fractions of 8 Gy) with ‘best supportive care’ and ‘best supportive care’ only. The primary endpoint is overall survival from randomization. Secondary endpoints include preservation of quality of life (EORTC-QLQ-C30 and -PAN26), NRS pain score response and WHO performance scores at baseline, and, 3, 6 and 12 months. Acute and late toxicity will be scored using CTCAE criteria version 5.0: assessed at baseline, day of last fraction, at 3 and 6 weeks, and 3, 6 and 12 months following SABR.

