To investigate whether SABR, in comparison to best supportive care, relieves tumor-related symptoms, enhances quality of life, and prolongs survival, patients will be randomized between either SABR with ‘best supportive care’ and ‘best supportive care’ only by the principal investigator or coordinating physician. Following the TwiCs design, patients allocated to the intervention arm receive an appointment with the radiation oncologist to confirm eligibility and subsequently are asked additional informed consent. Patients randomized in the control arm will not be approached since they gave informed consent for the PACAP cohort (see Fig. 1).

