To preserve safety and assess the hypothesis that SABR is safe and feasible in the intended population, an interim analysis will be conducted after 36 patients have completed the follow-up assessments after three months. This includes an epidemiological assessment of all adverse events (AE’s) and primary and secondary outcome measures. Using prior literature as reference, we have decided that the study will be halted in case of an incidence of grade ≥ 3 GI toxicity of > 20% in the intervention arm [11]. All grade > 2 AEs will be reported up to three months following SBRT, only the treatment induced grade > 2 AEs will be recorded up to the end of the study. The principal investigator or an authorized delegate will decide whether or not an AE is related to the SABR. If an AE has occurred, exact information on the time period, magnitude of the event and consequences for the patients will be investigated.

An independent data safety and monitoring committee (DSMB) has been assigned to examine safety parameters and evaluate the progress of the study. The DSMB consists of an independent epidemiologist/statistician (chairman), a radiation oncologist and a surgeon. All involved physicians will be repeatedly urged to report any potential AE’s. The monitoring committee will review and debate this list of AEs. To discuss a specific AE, the monitoring committee may call for a comprehensive report. A copy of this report will be sent to the involved physicians and the main ethics board.

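### Late grade 3 or higher events are recorded only if judged SABR-induced in an open design, so the late GI toxicity rate depends on an attribution that the recorded data cannot test

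*Protocol article*

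**What the plan says.** The recording rule is in Methods/design of the protocol article, in the paragraph on the interim analysis and adverse events. It has two periods.

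- Up to three months: "All grade > 2 AEs will be reported up to three months following SBRT", whatever the cause.
- After that: "only the treatment induced grade > 2 AEs will be recorded up to the end of the study".

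The same paragraph says who judges relatedness: "The principal investigator or an authorized delegate will decide whether or not an AE is related to the SABR". It mentions no independent or masked adjudication.

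The toxicity paragraph of Methods/design treats toxicity after three months as late, and says that "particular attention will be paid to complaints of the stomach or duodenum", giving dyspepsia, bleeding and perforation as examples. It describes the scoring in these words: "All radiation-associated early and late toxicity will be scored according to the NCI-CTCAE toxicity criteria version 5.0". The abstract schedules CTCAE toxicity as "assessed at baseline, day of last fraction, at 3 and 6 weeks, and 3, 6 and 12 months following SABR".

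Allocation is open. Randomization is done "by the principal investigator or coordinating physician", and "Patients randomized in the control arm will not be approached since they gave informed consent for the PACAP cohort".

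**The concern.** In the first three months, relatedness is a label on an event that is already in the database. After three months it becomes the condition for entering the event. The change comes exactly where attribution is hardest: in pancreatic cancer, a late bleed, perforation or dyspeptic complaint can plausibly arise from progression as well as from radiation. The person deciding can be expected to know that the patient had SABR.

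The trial is described as a phase 2 study giving preliminary outcomes for further studies, so its late GI safety result is something that later work would use. If the only late events on file are those already judged SABR-induced, nobody working from that file can ask how much the result depends on the judgement. The DSMB reviews a list of adverse events, and a late event judged unrelated need not be on it.

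**Working it through.** **1. The protocol's own figures.** The article gives no expected late toxicity rate, so there is none to reproduce. The figures used for the denominators are consistent.

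- Diluted survival: 0.7 × 50% + 0.3 × 20% = 41%, as stated.
- Sample size for 41% against 20%, two-sided alpha 15% and power 80%: 48.7 per arm by the arcsine formula and 50 by the usual two-proportion formula, against the stated 49.

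**2. How many patients the late rate rests on.** Inputs from the sample-size paragraph: 49 per arm, 30% of the intervention arm declining SABR, 50% of treated patients alive at 6 months. Exponential survival is my assumption.

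- Patients starting SABR: 49 × 0.7 = 34.3, about 34.
- Alive at 3 months from randomization: 34.3 × 0.5^(3/6) = 24.3, about 24.
- The cut-off, however, runs from SABR. The first fraction may come up to four weeks after consent and treatment may last up to 14 days, which puts the cut-off as late as about 4.5 months from randomization: 34.3 × 0.5^(4.5/6) = 20.4, about 20.
- Weight of one event: 1/24 = 4.2 points; 1/20 = 5.0 points.

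**3. Direction of the error.** Let r be the true rate of SABR-induced late grade 3 or higher events, b the rate of other such events, s the share of induced events judged induced, and f the share of other events judged induced.

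- Recorded rate = s·r + f·b.
- All-cause rate = r + b. The shortfall is (1 − s)·r + (1 − f)·b, which is never negative, so the recorded rate is always at or below the all-cause rate.
- Error against the SABR-induced rate = f·b − (1 − s)·r, which can have either sign.

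An illustration with assumed values, none of them from the documents: r = 10%, b = 20%.

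| s | f | Recorded | Error against induced (10%) | Error against all-cause (30%) |
|---|---|---|---|---|
| 0.5 | 0 | 5% | −5 points | −25 points |
| 0.75 | 0.2 | 7.5% + 4% = 11.5% | +1.5 points | −18.5 points |

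Over a wider grid (r = 10%, b = 10 to 30%, s = 0.5 to 1.0, f = 0 to 0.3) the recorded rate runs from 5% to 19%. The error is −5 to +9 points against the induced rate and −7 to −35 points against the all-cause rate.

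**4. Whether the safeguards sit before or after the filter.**

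- The 6- and 12-month CTCAE scoring is worded as covering radiation-associated toxicity, so it too depends on attribution.
- Committee review works from the list of adverse events.
- Monitoring verifies reported data against source; leaving out a late event judged unrelated complies with the protocol.
- Source data are kept for 15 years, so omitted events could be recovered, but only by a chart review that the article does not describe.

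**The case against.** The strongest reply is that a toxicity rate is meant to count treatment-induced events, so restricting late recording to those is deliberate, and an all-cause rate is a different quantity. Without late events from the control arm, an all-cause rate mixes progression with toxicity. The secondary endpoint in Methods/design is worded as acute and subacute toxicity, although the abstract names late toxicity as well. All of this stands. It limits the weight of the point, but it does not make the recorded rate testable.

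Three stronger readings are tempting, and the documents do not support them.

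- *A reader might infer that the late rate can only be too low.* That is certain only against the all-cause rate. Progression events wrongly ascribed to SABR push the rate up, and nothing in the article settles which error dominates.
- *A reader might infer that omitted events can never be re-checked.* Source documents are retained, monitoring visits use them, physicians are urged to report any potential adverse event, and the committee may ask for a full report on a specific one. The accurate statement is narrower: the recorded trial data alone do not allow it.
- *A reader might infer that the rule distorts the interim safety look.* The interim is triggered when 36 patients have completed their three-month assessments, and all grade > 2 events are reported up to three months after SABR. In that window attribution labels an event without removing it.

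Two smaller limits: knowledge of allocation is inferred from the open design and is not stated in so many words, and the judgement may be made by a delegate instead of the principal investigator.

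**Conclusion.** The point holds as a limited one about late safety data. After three months from SABR, a grade 3 or higher event is recorded only if an investigator in an open trial judges it SABR-induced. The late GI rate is therefore open to attribution bias, and its direction against the true SABR-induced rate is unknown. The recorded data give no all-cause late rate and no way to vary the attribution, and the DSMB would not see omitted events unless they were retrieved from source.

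With roughly 20 to 24 patients at the cut-off, each omitted event is worth about 4 to 5 points. This rests on the protocol's 30% refusal and 50% six-month survival, on exponential survival, and on the delay from randomization to the end of SABR. The size of any actual bias cannot be stated, because the article gives no late event rate. The primary endpoint and the sample size are not affected.

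**What to change.** For patients who start SABR, record every grade 3 or higher GI event to the end of the study regardless of attribution, and enter the relatedness judgement in a separate field. Use the CTCAE assessments already scheduled at 6 and 12 months. Because some patients will die before the 6-month assessment, accept events through the existing adverse-event reporting route as well. Reword the toxicity paragraph so that late scoring of these events is not confined to those considered radiation-associated.

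Report the late GI rate twice, as all-cause and as judged SABR-related, and show both to the existing DSMB.

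The cost is a few extra adverse-event entries in some 20 to 24 patients and one more table row, with no new visit, assessor or committee. The drawback is that the all-cause rate includes progression events and has no control-arm comparator. It should be labelled as an upper bound on late toxicity, not as an estimate of it.
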